## Abstract

**Background:**

Both dexamethasone and betamethasone, given to women at risk of preterm birth, substantially improve short-term neonatal health, increase the chance of the baby being discharged home alive, and reduce childhood neurosensory disability, remaining safe into adulthood. However, it is unclear which corticosteroid is of greater benefit to mother and child.

This study aims to determine whether giving dexamethasone to women at risk of preterm birth at less than 34 weeks’ gestation increases the chance of their children surviving free of neurosensory disability at two years’ corrected age, compared with betamethasone.

**Methods/Design:**

*Design* randomised, multicentre, placebo controlled trial.

*Inclusion criteria* women at risk of preterm birth at less than 34 weeks’ gestation with a singleton or twin pregnancy and no contraindications to the use of antenatal corticosteroids and who give informed consent.

*Trial entry & randomisation* at telephone randomisation eligible women will be randomly allocated to either the dexamethasone group or the betamethasone group, allocated a study number and corresponding treatment pack.

*Study groups* women in the dexamethasone group will be administered two syringes of 12 mg dexamethasone (dexamethasone sodium phosphate) and women in the betamethasone group will be administered two syringes of 11.4 mg betamethasone (Celestone Chronodose). Both study groups consist of intramuscular treatments 24 hours apart.

*Primary study outcome* death or any neurosensory disability measured in children at two years’ corrected age.

*Sample size* a sample size of 1449 children is required to detect either a decrease in death or any neurosensory disability from 27.0% to 20.1% with dexamethasone compared with betamethasone, or an increase from 27.0% to 34.5% (two-sided alpha 0.05, 80% power, 5% loss to follow up, design effect 1.2).

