#### Study groups

Once all entry details are given and eligibility is confirmed, the woman is randomised by contacting the central telephone randomisation service at the University of Adelaide. Assignment to one of two study groups: either the dexamethasone group or the betamethasone group will be stratified for collaborating centre, gestational age (<28 weeks’, ≥28 weeks’ gestation), and number of fetuses (1 or 2). A Study Number will be allocated to the woman corresponding to a treatment pack, each of which looks identical and contains two opaque study-labelled syringes.

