#### Sample size

With a predicted mortality rate of 6.05% up to two years and a predicted rate of neurosensory disability in survivors of 20.9%, we estimate the rate of our primary outcome of death or neurosensory disability at two years corrected age in an Australian/New Zealand population exposed antenatally to betamethasone to be 27.0% [3,37,43,44].

A trial of 1499 children, allowing 5% loss to follow up and with a design effect of 1.2 to allow for the clustering of babies within mothers, will have 80% power to detect a statistically significant difference at an alpha level of 0.05 (two-tailed) of either:

•a decrease in the combined outcome of death or neurosensory disability from 27.0% to 20.1% (Absolute Risk Difference (ARD) 6.9%; Relative Risk Difference (RRD) 25.6%) with dexamethasone compared with betamethasone, or;

•an increase from 27.0% to 34.5% (ARD 7.5%; RRD 27.8%).

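### The abstract requires 1449 children and the Methods 1499 on identical assumptions; 1499 reproduces, 1449 does not

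*Protocol article*

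**What the plan says.** The protocol article states the required number of children twice.

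- **Abstract, Methods/Design, sample size:** "a sample size of 1449 children is required to detect either a decrease in death or any neurosensory disability from 27.0% to 20.1"%, or an increase from 27.0% to 34.5%. The inputs follow in brackets: "two-sided alpha 0.05, 80% power, 5% loss to follow up, design effect 1.2".
- **Main text, Sample size:** "A trial of 1499 children, allowing 5% loss to follow up and with a design effect of 1.2" for the clustering of babies within mothers, and this number "will have 80% power to detect a statistically significant difference at an alpha level of 0.05 (two-tailed"). The alternatives are "a decrease in the combined outcome of death or neurosensory disability from 27.0% to 20.1"% and "an increase from 27.0% to 34.5% (ARD 7.5%; RRD 27.8"%).

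The control rate, both alternatives, alpha, sidedness, power, loss allowance and design effect agree. Only the total differs: 1449 in the abstract and 1499 in the main text.

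**The concern.** Both totals are current text, both are presented as the result of the same calculation, and the article offers nothing to reconcile them. At least one must be wrong.

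What is at stake is mainly the clarity of the prespecified target. With two published totals, a final count between 1449 and 1499 could be reported as meeting the target or missing it, depending on which part of the article is cited. The abstract is also the part most often read, and its sentence claims 80% power for the smaller number. It therefore matters which figure follows from the stated inputs, and how far the other falls short.

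**Working it through.** **Inputs.** From the Sample size section, repeated in the abstract: control rate p1 = 0.270; alternatives p2 = 0.201 and p2 = 0.345; two-sided alpha 0.05 (z = 1.960); power 80% (z = 0.842); loss 5%; design effect 1.2. Assumption: 1:1 allocation. The Study groups section describes two groups and gives no ratio.

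**Formula.** Pooled-variance comparison of two proportions without continuity correction, with p̄ = (p1 + p2)/2 and d = |p1 − p2|:

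n per arm = [1.960 × √(2p̄(1 − p̄)) + 0.842 × √(p1(1 − p1) + p2(1 − p2))]² / d²

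Total = 2 × n × 1.2 / 0.95

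**Reproducing the Methods figure.**

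| | 27.0% vs 20.1% | 27.0% vs 34.5% |
|---|---|---|
| d | 0.069 | 0.075 |
| p̄ | 0.2355 | 0.3075 |
| √(2p̄(1 − p̄)) | 0.6001 | 0.6526 |
| √(p1(1 − p1) + p2(1 − p2)) | 0.5981 | 0.6504 |
| Numerator | (1.1761 + 0.5034)² = 2.8206 | (1.2791 + 0.5474)² = 3.3361 |
| d² | 0.004761 | 0.005625 |
| n per arm | 592.4 | 593.1 |
| × 2 × 1.2 | 1421.9 | 1423.4 |
| ÷ 0.95 | **1496.7** | **1498.3** |

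The larger total, rounded up, is 1499, which is the Methods figure. If each arm is first rounded up to a whole number (593 and 594), the totals are 1498.1 and 1500.6, still within two children of 1499.

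**Can another convention give 1449?** Total children required, decrease and increase:

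| Variant | Decrease | Increase |
|---|---|---|
| Pooled, loss as × 1.05 | 1492.9 | 1494.6 |
| Pooled, loss omitted | 1421.9 | 1423.4 |
| Unpooled variance, ÷ 0.95 | 1489.8 | 1491.4 |
| Unpooled variance, × 1.05 | 1486.0 | 1487.7 |
| Arcsine, ÷ 0.95 | 1492.5 | 1496.3 |
| Arcsine, × 1.05 | 1488.7 | 1492.5 |
| Continuity correction, ÷ 0.95 | 1571.4 | 1566.3 |
| Continuity correction, × 1.05 | 1567.4 | 1562.4 |

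None gives 1449.

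**Power at each total.** The effective number per arm is N × 0.95 / 1.2 / 2. That is 573.6 for N = 1449 and 593.4 for N = 1499. Power is Φ([d√n − 1.960√(2p̄(1 − p̄))] / √(p1(1 − p1) + p2(1 − p2))).

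- N = 1449, decrease: (1.6525 − 1.1761) / 0.5981 = 0.797, power 78.7%.
- N = 1449, increase: (1.7962 − 1.2791) / 0.6504 = 0.795, power 78.7%.
- N = 1499, decrease: (1.6808 − 1.1761) / 0.5981 = 0.844, power 80.1%.
- N = 1499, increase: (1.8269 − 1.2791) / 0.6504 = 0.842, power 80.0%.

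**Detectable rates at 80% power.** With 1449 children, about 20.0% or 34.6% against 27.0%. With 1499, 20.1% or 34.5%, which are the stated alternatives.

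**The case against.** The best case on the other side is that this is a slip of one digit in an abstract, with the full Sample size section already correct, and that its consequence is negligible. Power falls by about 1.3 percentage points and each detectable rate moves by 0.1 point. That is small beside the uncertainty in the planning inputs. With 2% loss in place of 5%, for example, the requirement would be 1421.9 / 0.98 = 1450.9 or 1423.4 / 0.98 = 1452.5. Nothing suggests that recruitment would be stopped on the abstract's figure.

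It can also be said that the 80% depends on the method. With a continuity correction neither total reaches it: power is about 76.6% to 76.8% at 1449 and about 78.1% to 78.2% at 1499. Under the unpooled and arcsine formulas a few children fewer than 1499 would be enough.

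Most of this stands as a statement of size. The power effect is minor, and the claim that 1499 delivers 80% should be read as applying to the formulas without continuity correction. None of it removes the contradiction. Both places state 5% loss, so a smaller loss allowance cannot account for 1449, and neither can any other convention tried. That 1449 is a digit slip is plausible, but it is an inference.

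**Conclusion.** The point holds. The article gives two required totals for one set of assumptions. The 1499 in the Sample size section follows from them and the 1449 in the abstract does not. The abstract's figure is 50 children short and gives 78.7% power for either alternative, against the 80% claimed; 1499 gives 80.1% and 80.0%. This is a wrong headline number with a small effect on power, and not a serious lack of power. The conclusion rests on 1:1 allocation, which the article does not state, and on the two-proportion formula without continuity correction, which is the form that reproduces the Methods figure.

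**What to change.** Change the abstract to 1499 children so that it agrees with the Sample size section. If 1449 is in fact the target in use, change the Sample size section instead and restate the power in both places as about 78.7%. At the same time, confirm that the full protocol, the registry entry and any recruitment tracking carry the chosen number; none of these was available here, so this is a check and does not imply that they are wrong. The cost is a correction of one number, by erratum if need be. If 1499 is the target in use, nothing changes in the design, conduct or analysis.

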**Discussion:**

This study will provide high-level evidence of direct relevance for clinical practice. If one drug clearly results in significantly fewer deaths and fewer disabled children then it should be used consistently in women at risk of preterm birth and would be of great importance to women at risk of preterm birth, their children, health services and communities.

**Trial registration:**

Trial registration number:
ACTRN12608000631303

## Background

Children born preterm have a higher than average risk of dying in the first weeks of life and survivors experience higher rates of neurosensory disability than children born at term [1,2]. There is clear evidence that antenatal corticosteroids, both dexamethasone and betamethasone, given to women at risk of preterm birth substantially improve short-term neonatal health, increase the chance of the baby being discharged home alive, and reduce childhood neurosensory disability, remaining safe into adulthood [3]. The type of antenatal corticosteroid to use in clinical practice remains unclear [3]. Dexamethasone and betamethasone are both recommended [4] and widely used [1].

Is dexamethasone better than betamethasone, or vice versa? Our meta-analysis, using the limited data available from randomised trials that have directly compared the two treatments shows that dexamethasone reduces the risk of the baby developing intraventricular haemorrhage (IVH) to a greater extent than betamethasone [5]. While reduced IVH is a very important outcome, achieving a reduction in long-term survival free of any disability is the most important goal [2]. Data regarding the effects on long-term health are sparse.

### Preterm birth and antenatal corticosteroids

One of the major advances in maternal fetal medicine over the last 35 years has been the evaluation and implementation into clinical practice of administration of antenatal corticosteroids to women at risk of preterm birth [3]. Corticosteroids remain the ‘gold standard’ antenatal intervention to reduce the risk of fetal and neonatal mortality related to preterm birth.

Meta-analysis of the 21 randomised trials (14 using betamethasone, six using dexamethasone, one unknown, using a wide range of different treatment regimens, in 3885 women and 4269 infants) included in the Cochrane Systematic Review “Antenatal corticosteroids for accelerating fetal lung maturation” [3] shows that, compared with placebo, both dexamethasone and betamethasone have large and clinically substantial beneficial effects compared with controls on the risk of fetal and neonatal death, respiratory distress syndrome, intraventricular haemorrhage (IVH) and long-term neurological sequelae [3]. Thirty years after antenatal betamethasone treatment, health outcomes are generally good, apart from indirect evidence of possible mild insulin resistance [6], but there have been no follow-up studies of similar duration for dexamethasone.

Clinical practice guidelines for the use of antenatal corticosteroids have been developed by many colleges and institutions [7,8], often based on the NIH Consensus Panel Guidelines that were first released in 1994 [9], and again in 2000 [4]. These guidelines state that “All pregnant women between 24 and 34 weeks gestation who are at risk of preterm delivery within 7 days should be considered candidates for antenatal treatment with a single course of corticosteroids” [4].

### Corticosteroid type and regimen in current clinical practice

There is considerable variation between countries as to whether dexamethasone or betamethasone is used in clinical practice. There are likely to be many reasons for these differences including availability, costs [10] (dexamethasone is cheaper than betamethasone so is widely used in low-income countries), impact of non-randomised, observational studies on efficacy and safety [11,12] and influence of opinion leaders [13]. In Australia and New Zealand both preparations are used, betamethasone most frequently [14].

The optimal treatment regimen to use for antenatal corticosteroids is uncertain. The current Cochrane review “Antenatal corticosteroids for accelerating fetal lung maturation” presents no evidence on an optimal dosing regimen [3]. An earlier version of this Cochrane review [15] mentioned “a policy of administering corticosteroids (24 mg betamethasone, or 24 mg dexamethasone)”, without specifying treatment regimens in detail. The NIH Consensus Statement, based on information available in the late 1990s, recommended “two doses of 12 mg of betamethasone given intramuscularly 24 hours apart or four doses of 6 mg of dexamethasone given intramuscularly 12 hours apart” [4]. Since 2000 there have been four further trials, some using different treatment regimens, and these are now included in the Roberts systematic review with the review authors highlighting that “further research is required to determine the optimal dose to use” [3].

Given this uncertainty it is not surprising to find a variety of different treatment regimens used in clinical care. For instance, to complete a course of antenatal corticosteroids, 48% of practitioners in Australia and New Zealand prescribe two injections at 12 hour intervals and 43% prescribe two injections at 24 hour intervals, with variation for both dexamethasone and betamethasone [14]. Practice is similarly varied in the UK [16]. To complete a course of 24 mg dexamethasone over 24 hours, the treatment regimen varies between institutions, and even within institutions, and includes 8 mg for 3 doses 8 hours apart [17], 12 mg for two doses 12 hours apart [17,18], or 12 mg for two doses 24 hours apart [18,19].

### Evidence from non-randomised cohort studies using dexamethasone or betamethasone

There have been several recent non-randomised, retrospective human studies comparing antenatal dexamethasone and betamethasone [11,12,20-22], and particularly their effects on IVH and periventricular leukomalacia; both major precursors for cerebral palsy. Results are conflicting, with some studies reporting no differences in the risk of IVH [12,21,22], periventricular leukomalacia [11,21,22], or mortality [12,21,22], but others report that dexamethasone is associated with an increase in periventricular leukomalacia [12] and neurosensory impairment [20]. The inherent risk of bias with retrospective study designs should limit the conclusions drawn for clinical practice, but this caution is not always mentioned [11,13,20-22]. Furthermore, it is possible that some effects of dexamethasone on periventricular leukomalacia may be attributable to the sulphite preservative used in some formulations rather than the drug itself, as shown in a mouse model [23].

### Appraising the evidence - the cochrane review

#### Evidence from randomised controlled trials using dexamethasone or betamethasone: effect on childhood health - reduction in neurosensory disability

Five randomised trials (908 children) with long-term follow-up are included in the Roberts Cochrane systematic review; [3] three comparing antenatal betamethasone with placebo [24-26], and two comparing dexamethasone with placebo [27,28].

Compared with placebo, both antenatal dexamethasone and betamethasone were associated with less developmental delay in childhood (Relative Risk (RR) 0.49, 95% Confidence Interval (CI) 0.24 to 1.00, 2 trials, 518 children), and a trend towards fewer children having cerebral palsy (RR 0.60, 95% CI 0.34 to 1.03, 5 trials, 904 children) [3]. Authors in the Roberts’ review emphasise that their review does not suggest evidence of a difference in risk of cerebral palsy between betamethasone and dexamethasone. Highlighting this research gap they state “Future studies are needed to determine the optimal drug” [3].

#### Evidence from randomised trials: direct comparison of dexamethasone with betamethasone

We have conducted a Cochrane systematic review to assess the use of different corticosteroids and regimens for accelerating fetal lung maturation for women at risk of preterm birth [5].

Five trials met the inclusion criteria [29-33]. No health outcomes of relevance for the mother were reported from any of the trials. For the infant, antenatal exposure to dexamethasone was associated with a significantly lower risk of IVH than exposure to betamethasone (3.5% versus 6.9%, RR 0.44 95% CI 0.21 to 0.92, 4 trials, 717 infants). No significant difference was seen for respiratory distress syndrome, severe intraventricular haemorrhage, periventricular leukomalacia or death. Information on childhood outcomes is limited to a single trial that reported one instance of neurosensory disability among only 12 infants admitted to neonatal intensive care unit and followed up at 18 months [33].

We conclude from this systematic review that high quality randomised controlled trials comparing dexamethasone and betamethasone are needed. Trials must be adequately powered to be able to detect important differences, not only in neonatal outcomes but also in survival and health into childhood.

#### Aims and objectives of this trial

The primary aim of this randomised controlled trial is to determine whether giving antenatal dexamethasone to women at risk of preterm birth at less than 34 weeks’ gestation increases the chance of their children surviving free of neurosensory disability at two years’ corrected age, compared with women given antenatal betamethasone.

#### Hypotheses

The primary hypothesis of the study is that, compared with betamethasone, antenatal dexamethasone given to women at risk of preterm birth (less than 34 weeks’ gestation) reduces the risk of death or any neurosensory disability, caused by impairments such as cerebral palsy, blindness, deafness or developmental delay, in their children at two years’ corrected age.

The secondary hypotheses are that compared with betamethasone, antenatal dexamethasone treatment has benefits *up to the time of primary hospital discharge*, relating to: *the baby,* of neonatal morbidity; and *the mother,* of maternal infections, and quality of life; and *at two years’ corrected age,* relating to individual components of the primary outcome and body size, respiratory morbidity, blood pressure, behaviour and general health of the child.

## Methods/Design

### Ethics statement

Ethics approval was granted by the Children’s Youth and Women’s Health Services Human Research Ethics Committee at the Women’s and Children’s Hospital (REC2074/7/14) and by the local institutional review boards for each centre.

### Study design

Randomised, multicentre, placebo controlled trial.

#### Inclusion criteria

Women are eligible for the trial if they are at risk of preterm birth at less than 34 weeks gestation, have a singleton or twin pregnancy, no contraindications to the use of antenatal corticosteroids and give informed consent.

#### Exclusion criteria

Women are not eligible if they have chorioamnionitis requiring urgent delivery, a higher order multiple pregnancy, have already received antenatal corticosteroids, have known fetal lung maturation, or are in the second stage of labour.

### Trial entry

All eligible women will be given the trial information sheet, counselled by a member of the research team and encouraged to discuss the study with her family before written informed signed consent is sought.

#### Study groups

Once all entry details are given and eligibility is confirmed, the woman is randomised by contacting the central telephone randomisation service at the University of Adelaide. Assignment to one of two study groups: either the dexamethasone group or the betamethasone group will be stratified for collaborating centre, gestational age (<28 weeks’, ≥28 weeks’ gestation), and number of fetuses (1 or 2). A Study Number will be allocated to the woman corresponding to a treatment pack, each of which looks identical and contains two opaque study-labelled syringes.

##### Dexamethasone study group

Women randomised to the dexamethasone study group will receive the contents of the two syringes intramuscularly 24 hours apart, each containing 12 mg dexamethasone (as dexamethasone sodium phosphate - a non-sulphite containing preparation).

##### Betamethasone study group

Women randomised to the betamethasone study group will receive the contents of the two syringes intramuscularly 24 hours apart, each containing 11.4 mg betamethasone (as Celestone Chronodose 11.4 mg).

##### Both study groups

At weekly intervals, if the woman has not yet given birth, and remains at continued risk of preterm birth, justifying the use of repeat antenatal corticosteroids [34-36], a ‘repeat treatment pack’ containing a single syringe from the same treatment group will be allocated using the telephone randomisation service.

Care during the antenatal period, labour and postnatal stay will be managed by the obstetric team caring for the woman. Care of the neonate will be the responsibility of the attending neonatologist.

### Follow up after birth until the time of primary discharge for both groups

The pregnancy and labour data will be abstracted from case notes by the masked research assistant at the collaborating hospitals. The postnatal and neonatal data will be collected similarly after discharge of the mother and baby from hospital.

### Longer term follow up

Parents enrolled in the trial will give consent for follow-up of their children from birth until two years’ corrected age at the time of the initial, prenatal recruitment. Mothers of all babies discharged home alive will be contacted by a member of the study team from the coordinating centre by mail soon after their baby is discharged and then again when their baby is six, 12 and 18 months corrected age. Mothers will be provided with a reply paid envelope and asked to confirm their current contact details by mail. At each of these times, a member of the study team at the coordinating centre will contact the parents by telephone if a response has not been received in the mail.

